# Sitafloxacin- Versus Moxifloxacin-Based Sequential Treatment for Mycoplasma Genitalium Infections: Protocol for a Multicenter, Open-Label Randomized Controlled Trial

**DOI:** 10.2196/52565

**Published:** 2023-11-14

**Keywords:** bacteria, bacterial, clinical trial, clinical trials, controlled trials, doxycycline, drug, drugs, genital, genitalia, infection, medication, medications, moxifloxacin, Mycoplasma genitalium, pharmaceutic, pharmaceutical, pharmaceuticals, pharmaceutics, pharmacology, pharmacotherapy, pharmacy, quinolone resistance-associated mutation, randomized controlled trial, RCT, sexual transmission, sexually transmitted infection, sexually transmitted, sitafloxacin, STD, STI

## Abstract

**Background:**

*Mycoplasma genitalium* is an emerging sexually transmitted pathogen associated with increasing antibiotic resistance. The current treatment guidelines recommend moxifloxacin-sequential therapy for macrolide-resistant *M*
*genitalium* or strains with unknown resistance profiles. However, it is unclear whether sitafloxacin, a 4th-generation fluoroquinolone antibiotic, is effective against resistant strains.

**Objective:**

This study aims to assess and compare the efficacy and safety of sitafloxacin- and moxifloxacin-based treatment regimens for managing *M*
*genitalium* infections.

**Methods:**

We will conduct this randomized controlled trial at multiple centers in Japan. Eligible participants include adults aged 18 years or older with a confirmed *M*
*genitalium* infection, as determined through the nucleic acid amplification test. Patients will be randomly assigned using a stratified approach based on the treatment facility and infection site. The interventions comprise oral sitafloxacin (200 mg) daily for 7 days (with optional pretreatment of oral doxycycline, 200 mg, daily for up to 7 days), with a control group receiving oral doxycycline (200 mg) daily for 7 days followed by moxifloxacin (400 mg) daily for another 7 days. The primary outcome is the treatment success rate with a superiority margin of 10%, as confirmed through the nucleic acid amplification test. Secondary outcomes encompass changes in the bacterial load at the urogenital or rectal sites and the emergence of posttreatment-resistant mutant strains.

**Results:**

Enrollment commenced in June 2023 and will conclude in December 2024, with findings anticipated by 2025. The expected success rates fall within the range of 80% for sitafloxacin and 42% for moxifloxacin against *M*
*genitalium* carrying the G248T (S83I) mutation, based on previous studies. Accordingly, with a 5% significance level (2-sided) and 80% statistical power, we aim to recruit 50 participants per group, factoring in a 10% expected dropout rate.

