### Randomization and Blinding

We will use a computer-based stratified randomization approach to ensure an equitable allocation of participants across different treatment groups, stratifying based on 2 factors: the facility where the study participants are enrolled and the anatomical site of *M genitalium* infection (categorized as the urethra, rectum, or a combination of both). Participants will be randomly assigned to groups at a 1:1 ratio. Blinding will not be implemented, as treatment success will be determined using the NAAT, an objective test. After randomization, patients will receive their respective treatments and will be scheduled for a follow-up test of cure 3 weeks after completing the regimen, with a permissible range of 10-100 days. The test-of-cure content of the positive sites will be assessed using the NAAT. When treatment fails, the number of short tandem repeats in the protein MG309 will be analyzed to differentiate a new infection from a persistent one, as previously reported [26].

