### Statistical Analysis

The sample size has been determined based on previous treatment success rates and specific assumptions. In a preliminary study, we determined that sitafloxacin achieved a treatment success rate of 92.9% against *M genitalium* with the *parC* G248T (S83I) mutation, in conjunction with wild-type *gyrA* [20]. Furthermore, sitafloxacin demonstrated a 78.9% success rate against strains carrying the *parC* G248T (S83I) mutation based on our preliminary data, and Murray et al [27] reported a moxifloxacin success rate of 41.2% against such strains. Accordingly, the success rates of sitafloxacin and moxifloxacin were anticipated to be 80% and 42%, respectively. With a 5% significance level (2-sided) and 80% statistical power for precise analysis, we aimed to enroll 50 participants per group (totaling 100 cases), considering the prevalence of the G248T mutation. Additionally, an expected dropout rate of approximately 10% was factored in, leading to a calculated sample size of 112 participants, evenly distributed across treatment groups, to robustly assess the efficacy of sitafloxacin and moxifloxacin against specific mutations in *M genitalium*.

Primary analyses regarding efficacy primarily rely on the full analysis set (FAS), which encompasses all registered participants, excluding ineligible participants and those not receiving the study drugs. To evaluate sensitivity, the analysis will be conducted for the per-protocol set, which consists of the study population, excluding cases of major protocol violations and discontinuations from the FAS. To evaluate safety, the analysis will be conducted for the safety analysis set, which includes all registered participants except those not receiving the study drug. Baseline characteristics of the study participants, both discrete and continuous, will be summarized. Discrete data will be presented as frequencies and percentages, whereas continuous data will be presented as descriptive statistics such as the mean and SD. Data will be analyzed with STATA (version 16.0; StataCorp), SAS software (version 9.4; SAS Institute), and R (version 4.1.2; R Foundation for Statistical Computing); the sample size calculation was done using Power Analysis and Sample Size 2022 (NCSS Statistical Software).

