### Efficacy Outcome

The primary outcome is the treatment success rate, defined as the absence of the pathogen, as indicated through the NAAT. We set the superiority margin at 10%. The secondary outcomes include the change in bacterial load from pre- to posttreatment and the emergence of posttreatment nucleotide polymorphisms in mutant strains compared with those in pretreatment samples. The bacterial load will be measured as previously reported [28]. For the primary outcome in the FAS, with or without the G248T (S83I) mutation, rates and their 95% CIs will be computed. The chi-square test will be used to assess the statistical significance of treatment success between groups. This primary analysis will also be conducted for participants with the G248T mutation in the per-protocol set. In terms of secondary endpoints, differences, and rates of change in the bacterial load will be analyzed using either the 2-tailed Student *t* test or the Mann-Whitney *U* test. The rate and 95% CI of posttreatment resistance mutations in the FAS group will also be estimated using the positive cure confirmation results.

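### The abstract and the Methods give different enrolment targets: 100 with the 10% dropout already inside, or 112 with it added on top

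*Protocol article*

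**What the plan says.** The abstract (Results paragraph) gives the recruitment aim as "we aim to recruit 50 participants per group, factoring in a 10% expected dropout rate". Read plainly, 50 per group is the number recruited and the dropout allowance is already inside it.

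The Methods (Statistical Analysis) build the number in two steps. First, "we aimed to enroll 50 participants per group (totaling 100 cases), considering the prevalence of the G248T mutation". Then, as an addition to that, "an expected dropout rate of approximately 10% was factored in, leading to a calculated sample size of 112 participants, evenly distributed across treatment groups". Here 50 per group comes before dropout, and the final figure is 112.

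The two places share their design inputs. The Methods state that "the success rates of sitafloxacin and moxifloxacin were anticipated to be 80% and 42%, respectively", and the error rates are given as "With a 5% significance level (2-sided) and 80% statistical power for precise analysis". The Efficacy Outcome section sets a superiority margin of 10%, and allocation is 1:1 (Randomization and Blinding).

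**The concern.** The same 50 per group includes dropout in one place and excludes it in the other, and both cannot be the target. The abstract does not merely leave out the inflation step; it says that the step is already contained in the 50. The Methods do not fully separate the two figures either, because they speak of enrolling the 100 before they arrive at 112.

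The target determines when recruitment stops, and the article reports that enrolment has begun. If recruitment stopped at 100 when 112 was intended, the trial would lose about a tenth of its evaluable participants. If 100 was the approved number, the 112 in the Methods is wrong.

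**Working it through.** **Inputs.** 50 per group and 10% dropout (abstract and Statistical Analysis); 112 in total (Statistical Analysis); 80% v 42% success, two-sided 5%, 80% power (Statistical Analysis); 10% margin (Efficacy Outcome); 1:1 allocation (Randomization and Blinding).

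**1. The Methods figure.** 50 / (1 − 0.10) = 55.6, rounded up to 56 per group; 2 × 56 = 112. The stated 112 reproduces exactly. Expected evaluable: 56 × 0.90 = 50.4, about 50 per group.

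**2. The abstract figure.** Enrolled: 2 × 50 = 100. Expected evaluable: 50 × 0.90 = 45 per group.

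**3. The gap.** Enrolled: 112 − 100 = 12. Evaluable: 2 × (50 − 45) = 10.

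**4. Do the inputs show which reading is right?** They do not. The number per group for 80% power at two-sided 5% depends on the method:

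| Method | n per group |
|---|---|
| No margin, pooled chi-square | 25 |
| No margin, continuity-corrected or Fisher exact | 30 |
| 10% margin, unpooled variance | 41 |
| 10% margin, Farrington-Manning | 45 |
| 10% margin, pooled null variance | 46 |
| 10% margin, continuity-corrected or fully pooled | 48 |

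The 45 from Farrington-Manning gives 45 / 0.90 = 50, which fits the abstract. The 48 lies within two of 50 before dropout, which fits the Methods. The article does not name the method, so neither match is proof.

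**5. Power against the 10% margin, all evaluable participants at 80% v 42%** (unpooled normal approximation):

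power = Φ[(0.80 − 0.42 − 0.10) / SE − 1.96], with SE = √[(0.80 × 0.20 + 0.42 × 0.58) / n] = √(0.4036 / n)

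- n = 45: SE = 0.0947; 0.28 / 0.0947 − 1.96 = 0.997; power 84%.
- n = 50: SE = 0.0898; 0.28 / 0.0898 − 1.96 = 1.157; power 88%.

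**6. Power in G248T carriers only, no margin** (chi-square without continuity correction, exact enumeration, 80% v 42%). The article gives no G248T prevalence, so the carrier share is an assumption and is varied. The 68.3% is the proportion with any *parC* mutation quoted in the Introduction, used here only as a proxy.

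| Assumed carrier share | Carriers per group, 45 v 50 evaluable | Power |
|---|---|---|
| 50% | 22–23 v 25 | 75–78% v 83% |
| 60% | 27 v 30 | 83% v 87% |
| 68.3% | 31 v 34 | 89% v 92% |
| 100% | 45 v 50 | 97% v 98% |

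Power is 78% at 23 carriers per group and 81% at 24, so 24 are needed. That is 24 / 45 = 53% of the evaluable participants under the abstract and 24 / 50 = 48% under the Methods. Only between these two shares does the choice of target decide whether this test reaches 80%.

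**7. Power in carriers against the 10% margin** (formula of step 5). At 68.3% carriers it is 69% v 73%; at 50% it is about 54–56% v 60%. Both targets fall short of 80% here, so the discrepancy is not the cause.

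**The case against.** The strongest reply is that the Methods contain the only full sample-size statement, that it ends on an explicit and arithmetically correct 112, and that the abstract sentence is a compression that merged the 50 with the dropout clause. Much of this stands. The target is not undefined: it is ambiguous between two stated numbers, and 112 is the more fully argued of them. It does not remove the contradiction, because the abstract states that dropout is inside the 50, and the Methods themselves attach enrolment to the 100.

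A reader might go further and infer that stopping at 100 would take the trial below its stated 80% power. The documents do not support that. It follows for carriers if they are taken to be 50% of participants and tested without a margin, but the article states neither that share nor a zero-margin calculation; what it says is "We set the superiority margin at 10" percent. At 60% or 68.3% carriers the no-margin power stays above 80% under both targets, as does the margin-based power with all participants counted.

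A reader might also conclude that 112 must be correct. That is plausible, but step 4 of the working shows that the inputs fit either reading.

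**Conclusion.** Wrong as written, of minor severity. The contradiction rests on the two statements alone and needs no assumption: 100 enrolled and about 45 evaluable per group, against 112 enrolled and about 50 evaluable per group.

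The consequence is modest. The lower target costs about four percentage points of power against the margin, provided that all evaluable participants count and the 80% v 42% rates apply to all of them; the article derives those rates for the G248T mutation. A drop below 80% caused by the lower target, in carriers tested without a margin, requires a carrier share between about 48% and 53%; below 48% both targets fall short. No analysis or estimand changes. How the base of 50 was derived is a separate question.

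**What to change.** The sponsor confirms the approved target, then states one enrolled and one evaluable number in both the abstract and the Statistical Analysis section.

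- If the Methods are right: 56 randomised and 50 evaluable per group, 112 in total, and the abstract is corrected.
- If 100 is right: 50 randomised and 45 evaluable per group, and the 112 in the Methods is corrected.

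In either case the enrolment verb should be attached only to the number that includes dropout. The cost is a one-line correction, with no participants beyond the Methods figure.

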**Conclusions:**

This study will provide valuable insights into the efficacy and safety of sitafloxacin- versus moxifloxacin-based sequential therapy in treating *M*
*genitalium* infections. These findings have the potential to influence clinical guidelines, favoring more effective therapeutic choices. The multicenter approach enhances the robustness of this study. However, a limitation is the potential insufficiency of statistical power to detect posttreatment-resistant mutant strains in each group, rendering posttreatment-resistance mutations a notable concern. In the future, we may need to increase the sample size to enhance power.

**Trial Registration:**

Japan Registry of Clinical Trials (jRCTs031230111); https://jrct.niph.go.jp/en-latest-detail/jRCTs031230111

**International Registered Report Identifier (IRRID):**

DERR1-10.2196/52565

## Introduction

The increase in the number of resistant strains of *Mycoplasma genitalium* is a global concern. The global prevalence of *M genitalium* in the general population ranges from 1.3% to 3.9% [1]. The prevalence of macrolide resistance-associated mutations (MRMs) has increased over the decades [2]. Furthermore, regional variations in resistant strains have been observed, with the prevalence of MRMs in the American and Western Pacific regions exceeding that in European countries [2]. The prevalence of quinolone resistance-associated mutations (QRAMs) has been increasing in the Western Pacific regions, including Australia, New Zealand, China, and Japan, making these regions focal points for resistance mutations [3-7]. The current national guidelines recommend resistance-guided sequential therapy for *M genitalium* infections when macrolide resistance testing is available; otherwise, empiric sequential therapy is recommended, commencing with doxycycline followed by fluoroquinolone [8-11]. For macrolide-susceptible strains, sequential therapy involves an initial cycle of doxycycline treatment followed by azithromycin, whereas for macrolide-resistant strains, it entails an initial cycle of doxycycline treatment followed by fluoroquinolone. According to Australian studies, resistance-guided therapy with doxycycline followed by azithromycin attains a high efficacy of 92% to 95.4% against macrolide-susceptible strains, whereas doxycycline followed by moxifloxacin achieves a high efficacy of 95.4% against macrolide-resistant strains, and doxycycline followed by sitafloxacin demonstrates a high efficacy of 95% against macrolide-resistant strains [12-14]. However, the cure rate of fluoroquinolone-based therapies depends on the prevalence of QRAMs, which include *parC* and *gyrA* mutations. Specifically, S83 and D87 mutations in *parC*, as well as M95, G93, and D99 mutations in *gyrA*, have been linked to treatment failure with moxifloxacin and sitafloxacin [15-19]. Additionally, combined *parC* and *gyrA* mutations limit the efficacy of fluoroquinolone-based therapy more significantly than single mutations [19,20]. As sitafloxacin, a newer-generation fluoroquinolone, is not widely available, direct comparisons between moxifloxacin and sitafloxacin treatments are lacking. Sitafloxacin exhibits higher efficacy against QRAM-resistant strains [14,17,18] and demonstrates a lower minimum inhibitory concentration relative to moxifloxacin in QRAM-resistant strains based on minimum inhibitory concentration assays [17,18]. Murray et al [14] conducted a clinical study and demonstrated that sitafloxacin-based sequential therapy for the most common *parC* G248T (S83I) mutant strains achieved a higher success rate than moxifloxacin-based sequential therapy. However, as previously mentioned, they did not directly compare the 2 drugs but instead retrospectively compared them at different times. Given the fluctuating numbers of mutant-resistant strains in recent years, a randomized clinical trial would be a more suitable approach to investigate the efficacy of these 2 drug regimens [14,21].

In Japan, the prevalence of resistant strains is high [3,21]. Ando et al [3] reported that 89.6% of strains harbored MRMs, with 68.3% harboring *parC* mutations and 27% harboring *gyrA* mutations. Given the unavailability of resistance testing for MRMs and the high prevalence of strains harboring MRMs (89.6%), sitafloxacin is the preferred treatment for *M genitalium* infections at our facility. Ando et al [20] reported that sitafloxacin monotherapy cleared strains harboring wild-type *parC* and *gyrA*. In addition to resistant strains, sitafloxacin demonstrated high effectiveness (92.9%) in clearing strains harboring *parC* G248T (S83I) mutations and wild-type *gyrA*, with 41.7% of those harboring *parC* G248T (S83I) and *gyrA* mutations. In contrast, moxifloxacin-based therapy cleared 96.5% of the strains harboring wild-type *parC* and *gyrA* [19]. The regimens mainly comprised sequential therapy with doxycycline followed by moxifloxacin and combination therapy with doxycycline and moxifloxacin. However, for strains harboring *parC* G248T (S83I) mutations and wild-type *gyrA*, the effectiveness of moxifloxacin-based therapy was limited to 54.2%. For those harboring *parC* G248T (S83I) and *gyrA* mutations, the effectiveness was further reduced to 18.8% [19]. Both sitafloxacin and moxifloxacin are newer-generation quinolones that exhibit a comparable incidence of gastrointestinal side effects [22,23]. These agents are less frequently associated with tendon rupture than levofloxacin, a prevalent fluoroquinolone drug [24]. Considering that both are broad-spectrum antibiotics, their impact on de novo resistance and the environment remains unclear and requires vigilant monitoring. A 7-day course of doxycycline is generally used to treat sexually transmitted infections with mild side effects, such as gastrointestinal disturbances [25].

Accordingly, we propose to conduct a multicenter, open-label randomized controlled trial aimed at comparing the efficacy and safety profiles of sitafloxacin and standard moxifloxacin-based sequential treatments in managing highly resistant *M genitalium* infections.

## Methods

### Study Design

This study constitutes a comparative randomized open-label parallel-group trial assessing the efficacy of sitafloxacin- versus moxifloxacin-based sequential treatment for *M genitalium* infections, particularly those involving resistant strains.

### Population and Eligibility Criteria

Participants are currently being recruited at the Sexual Health Clinic, AIDS Clinical Center of the National Center for Global Health and Medicine, and Personal Health Clinic in Japan (Figure 1). The inclusion criteria include several aspects. First, participants must be adults aged 18 years or older. Second, the confirmation of the presence of *M genitalium* in an individual’s urine or rectal samples is required through the nucleic acid amplification test (NAAT). Lastly, participants are obligated to provide written informed consent to partake in the study, with exclusion criteria covering individuals with known allergies to the study medications and pregnant women. Additionally, individuals deemed unsuitable for study participation by the attending physician based on various criteria or medical judgments will be excluded. Study participants who need antibiotics that are potentially effective for *M genitalium* infection. This includes quinolones other than the study drugs, as well as minocycline, pristinamycin, and nitroimidazole.

**Figure 1 figure1:**
[figure not shown]
Study flow chart.

### Randomization and Blinding

We will use a computer-based stratified randomization approach to ensure an equitable allocation of participants across different treatment groups, stratifying based on 2 factors: the facility where the study participants are enrolled and the anatomical site of *M genitalium* infection (categorized as the urethra, rectum, or a combination of both). Participants will be randomly assigned to groups at a 1:1 ratio. Blinding will not be implemented, as treatment success will be determined using the NAAT, an objective test. After randomization, patients will receive their respective treatments and will be scheduled for a follow-up test of cure 3 weeks after completing the regimen, with a permissible range of 10-100 days. The test-of-cure content of the positive sites will be assessed using the NAAT. When treatment fails, the number of short tandem repeats in the protein MG309 will be analyzed to differentiate a new infection from a persistent one, as previously reported [26].

### Intervention

In the intervention group, participants will be administered 200 mg of oral sitafloxacin daily for 7 days. Additionally, 200 mg oral doxycycline daily for up to 7 days will be administered as pretreatment, depending on the severity, before the definitive diagnosis of *M genitalium*. Severity will be assessed based on patients’ complaints.

In the control group, participants will be initially administered 200 mg oral doxycycline daily for 7 days, followed by 400 mg moxifloxacin daily for another 7 days.

### Statistical Analysis

The sample size has been determined based on previous treatment success rates and specific assumptions. In a preliminary study, we determined that sitafloxacin achieved a treatment success rate of 92.9% against *M genitalium* with the *parC* G248T (S83I) mutation, in conjunction with wild-type *gyrA* [20]. Furthermore, sitafloxacin demonstrated a 78.9% success rate against strains carrying the *parC* G248T (S83I) mutation based on our preliminary data, and Murray et al [27] reported a moxifloxacin success rate of 41.2% against such strains. Accordingly, the success rates of sitafloxacin and moxifloxacin were anticipated to be 80% and 42%, respectively. With a 5% significance level (2-sided) and 80% statistical power for precise analysis, we aimed to enroll 50 participants per group (totaling 100 cases), considering the prevalence of the G248T mutation. Additionally, an expected dropout rate of approximately 10% was factored in, leading to a calculated sample size of 112 participants, evenly distributed across treatment groups, to robustly assess the efficacy of sitafloxacin and moxifloxacin against specific mutations in *M genitalium*.

Primary analyses regarding efficacy primarily rely on the full analysis set (FAS), which encompasses all registered participants, excluding ineligible participants and those not receiving the study drugs. To evaluate sensitivity, the analysis will be conducted for the per-protocol set, which consists of the study population, excluding cases of major protocol violations and discontinuations from the FAS. To evaluate safety, the analysis will be conducted for the safety analysis set, which includes all registered participants except those not receiving the study drug. Baseline characteristics of the study participants, both discrete and continuous, will be summarized. Discrete data will be presented as frequencies and percentages, whereas continuous data will be presented as descriptive statistics such as the mean and SD. Data will be analyzed with STATA (version 16.0; StataCorp), SAS software (version 9.4; SAS Institute), and R (version 4.1.2; R Foundation for Statistical Computing); the sample size calculation was done using Power Analysis and Sample Size 2022 (NCSS Statistical Software).

